### Data management

All data collected will be de-identified and aggregated prior to analysis.

To ensure the quality of data from printed questionnaires, data entry and data quality validation will be performed by two researchers.

Secure systems with encryption and password protection will be used to store databases, and strong, unique passwords will be assigned. To minimize the risk of data loss, periodic backups will be performed and stored in separate information systems. Access to data prior to de-identification and aggregation will be limited to the research team, unless participants provide additional informed consent for individual access.

### Statistical analysis

Data analysis and reporting will be performed in accordance with CONSORT guidelines.

Analysis of the primary outcome will include all randomized participants, following an ITT approach.

Baseline characteristics, by group, will be reported using descriptive statistics and compared by χ2 and t-test for independent samples (or equivalent non-parametric test). To evaluate the effectiveness of the intervention, the proportion of participants with a decrease in depression severity symptoms category according to the BDI-II (main outcome) will be compared between control and intervention groups using generalised linear mixed models.

Further adjustment for relevant covariates, as supportive analysis, will be made. Secondary analyses include between-group differences over time in symptoms of depression, considering the BDI-II as a continuous variable. Regarding specific objectives, the analysis of symptoms of depression (BDI-II scale score) given the levels of CRP and IL-6 will be conducted using linear mixed models, adjusted for age, BMI, hemoglobin HbA1C, medication, physical activity, smoking and drinking habits and sex. The same method will be applied to test the effect of adherence to MedDiet on the levels of the biomarkers (CRP and IL-6) and in health-related quality of life. The association between adherence to MedDiet and changes in symptoms of depression will also be investigated, using, for this purpose, generalized linear mixed models. The economic cost-effectiveness of dietary counselling as an adjuvant treatment for MDD, compared to the usual treatment, will be presented as an incremental cost-effectiveness ratio, given the differences in the total costs of each treatment and their health effects (i.e., the proportion of patients with improvement in symptoms of depression after 12 weeks of intervention). For each outcome, results for either intervention and control group, and estimates of effect size with a 95% confidence interval will be reported. All analyses will be performed assuming a significance level of 5%.

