### Allocation and randomization

To ensure that the allocation of participants to the intervention and control arms is adequately done, a computer-generated list of random numbers will be used, stratified by centre, in variable blocks of sizes 2, 4, and 6. The treatment allocation will be concealed from the researchers and will be done using sequentially numbered, opaque, sealed envelopes. This will help prevent bias in the allocation process and ensure the validity of the study results. The researchers responsible for preparing the allocation sequence and the envelopes used in the randomization process will not have contact with the participants.

To maximize enrollment and retain participants, training and information about the trial will be provided to the medical doctors involved in recruitment through meetings, flyers, and emails. In addition, the consultations will be scheduled at times that are convenient for participants and will take place near their typical healthcare appointments. This will help minimize the burden of participation and promote retention to the study.

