### Sample size

Considering a two-sided significance level of 5% and a power of 80% and using data from the trial published by Jacka et al. [24], the minimum sample size required to detect a difference of 20% points in the proportions of participants with a decrease in the severity of depressive symptoms, between control and intervention groups (8 and 28%, respectively), after 12 weeks, is 114 participants (57 per arm). Such difference corresponds to an odds ratio of 4.5, considered clinically relevant and smaller than the effect size derived from the SMILES trial [24]. Taking into consideration an attrition of 40% at the end of the intervention, the minimum sample size estimated is 190 (95 per arm). Estimating a prevalence of elevated inflammation in 30% of MDD patients and 10% of patients that don’t meet other inclusion criteria, the number of recruited participants estimated is 700 [2, 9].

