### Intervention

Participants randomly allocated to the intervention group will attend six nutrition appointments with a duration between 30 and 60 min, in one of the participating centres of the trial, performed by a registered nutritionist in weeks 1, 2, 4, 6, 8 and 10. The intervention will promote adherence to the MedDiet without specific recommendations for weight change or calorie intake control.

Registered nutritionists involved in the intervention will participate in the baseline assessment but not in data collection at 12 weeks or at any of the follow-up assessments.

Both groups will maintain the TAU for MDD.

This trial will use a passive control group, with no active intervention apart from TAU.

All participants will have to be medicated with an antidepressant at the beginning of the trial. Changes in pharmacotherapy, including medicines and/or dosages, and additional treatments provided to participants (e.g., psychotherapy) will be documented and taken into consideration during statistical analysis.

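### The primary model should name baseline BDI-II and centre: the article makes covariate adjustment supportive and names neither, a small loss of efficiency rather than a validity error

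*Protocol article*

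**What the plan says.** All references are to the protocol article.

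- **Allocation and randomization:** "a computer-generated list of random numbers will be used, stratified by centre, in variable blocks of sizes 2, 4, and 6".
- **Main outcome:** success is a fall of at least one BDI-II severity category. The categories are 0–13, 14–19, 20–28 and 29–63, and entry requires a score above 13.
- **Statistical analysis:** "the proportion of participants with a decrease in depression severity symptoms category according to the BDI-II (main outcome) will be compared" between arms by generalised linear mixed models. No fixed or random terms are listed. The next sentence is "Further adjustment for relevant covariates, as supportive analysis, will be made". The only covariate list in the section (age, BMI, HbA1c, medication, physical activity, smoking and drinking, sex) belongs to the biomarker objectives. It contains neither centre nor baseline BDI-II.
- **Intervention:** changes in medication and "additional treatments provided to participants (e.g., psychotherapy) will be documented and taken into consideration during statistical analysis". The place of these changes in the analysis is not given.
- **Sample size:** an unadjusted comparison of two proportions, "between control and intervention groups (8 and 28%, respectively), after 12 weeks, is 114 participants (57 per arm").

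**The concern.** The endpoint is a step across a cut-off. A participant one point above a boundary needs a far smaller improvement to count as a success than one at the top of the same band. Baseline score is therefore prognostic by construction, and chance imbalance between arms in distance to the cut-off passes into an unadjusted estimate. Centre is the stratum of the randomisation. Leaving a stratum out of the analysis makes the standard error too large when centres differ in success rate. Ranking adjustment as supportive gives up this information in the result that decides the trial.

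A related loose end is that treatment changes after randomisation are to be considered in the analysis without saying in which one. In an open-label trial the intervention may influence these changes, so conditioning the primary effect on them could bias it.

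**Working it through.** **1. The plan's own figure.** Inputs from Sample size: two-sided 5%, 80% power, 8% against 28%. With p̄ = 0.18 and pooled variance under the null:

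n = [1.96·√(2·0.18·0.82) + 0.8416·√(0.08·0.92 + 0.28·0.72)]² / 0.20² = (1.0649 + 0.4415)² / 0.04 = 56.7, so 57 per arm.

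Power at 57 per arm is 0.802. The odds ratio is (0.28/0.72)/(0.08/0.92) = 4.47, and 114/0.6 = 190. The stated 57, 114, 190 and 4.5 all reproduce. They come from an unadjusted formula, so an unadjusted analysis delivers the planned power.

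**2. How success depends on the baseline score.** The documents give no distribution for BDI-II. Assume for illustration a control mean at follow-up of 24.5 + 0.6·(baseline − 28), which is a fall of 3.5 points at a baseline of 28, with residual SD 8. Success means a score at or below the top of the next lower band, with a half-point correction:

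| Baseline | Follow-up mean | Must be at or below | P(success), control |
|---|---|---|---|
| 19 | 19.1 | 13 | Φ(−5.6/8) = 24% |
| 20 | 19.7 | 19 | Φ(−0.2/8) = 49% |
| 28 | 24.5 | 19 | Φ(−5.0/8) = 27% |
| 29 | 25.1 | 28 | Φ(3.4/8) = 66% |

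The relation is a saw-tooth, so a linear baseline term captures little of it. In simulations of this scenario (baseline mean 28, SD 8, truncated above 13; 5-point effect; 57 per arm), power for the category endpoint was 71% unadjusted, 71% with a linear baseline term, and 73% with baseline category plus distance to the cut-off.

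**3. Power at the plan's own rates.** Simulated logistic models with likelihood-ratio tests: 114 participants, three equal centres, marginal rates 8% and 28%, 2,000 runs per setting. Covariate effects are assumed, and baseline is a generic prognostic score.

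| Baseline log-odds per SD | Centre SD (logit) | Unadjusted | + centre | + centre and baseline |
|---|---|---|---|---|
| 0 | 0 | 0.838 | 0.839 | 0.836 |
| 0 | 0.5 | 0.846 | 0.854 | 0.849 |
| 0.5 | 0.5 | 0.835 | 0.842 | 0.857 |
| 1 | 0.5 | 0.829 | 0.835 | 0.878 |
| 1 | 1 | 0.820 | 0.850 | 0.891 |

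Centre alone adds about 0 to 3 points. Centre and baseline together add about 0 to 7 (0.891 − 0.820 = 0.071). Monte Carlo error is about 0.008. Type I error was 0.046–0.056 unadjusted and 0.054–0.063 fully adjusted, so a little of the gain reflects a slightly liberal test at this sample size.

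**4. Level of the test if centre is ignored.** Three centres, 19 per arm in each, no treatment effect, pooled z test:

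| Centre success rates | Type I error |
|---|---|
| 4/8/12% | 4.5–4.7% |
| 2/6/16% | 4.3–4.4% |
| 8/18/28% | 4.7% |
| 20/40/60% | 3.6–3.8% |
| 10/40/70% | 2.1–2.3% |

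Ranges are over repeated simulations. A centre-stratified test gave 4.9–5.2% in the last two rows. The first three rows are on the scale of the planned rates. The last two assume a mean of 40% and very wide differences between centres.

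**The case against.** The strongest reply is that the article does not say centre is left out. A mixed model has random effects, none are listed, and centre is a natural candidate. The word "further" in the sentence on adjustment can mean beyond the design factors. Full lists of model terms usually sit in an analysis plan, which is not shown, and an unadjusted primary analysis matches the way the trial was sized.

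Most of this stands. A reader might infer that the primary analysis omits the randomisation stratum, that its standard error is materially wrong, or that power falls short. The text does not establish the first, and the figures above do not support the other two. What remains is that the article does make a choice: it labels covariate adjustment supportive, and it names neither variable for the primary comparison.

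A reader might also infer that medication changes and added psychotherapy will enter the primary model. The Intervention section does not say so, and Statistical analysis lists medication only in the biomarker models. The wording leaves the matter open and no more.

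It can also be said that the gains rest on assumed effects. That is correct. The saw-tooth scenario has control success far above the planned 8%. A larger gain for continuous BDI-II (81% to 90% in one simulation) concerns a secondary analysis and is not evidence about the primary one.

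**Conclusion.** The point holds as a free improvement. The article ranks covariate adjustment as supportive and does not name baseline BDI-II or centre in the primary model, although the endpoint is tied to the baseline score and centre is the randomisation stratum. The cost is about 0 to 7 points of power under assumed covariate effects. If centre is in fact ignored, the type I error is about 4.3 to 4.7% near the planned rates and falls to 2–4% only when centres differ very widely. The error is on the conservative side, so there is no added false-positive risk. The planned 80% power is not compromised. The textual point is firm; the sizes depend on the assumptions shown.

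**What to change.** In Statistical analysis, state that the primary generalised linear mixed model includes:

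- arm, with the 12-week arm contrast as the test;
- centre, with small later-added units pooled by a rule fixed in advance;
- baseline BDI-II, entered as baseline category plus distance to its cut-off rather than as a linear term alone.

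Report a standardised (marginal) risk difference. Adjustment in a logistic model changes the odds ratio from marginal to conditional, while the sample size rests on a difference in proportions. Make the unadjusted comparison the supportive result, and keep other covariates supportive. Keep the term list short: at the planning rates only 57·0.08 + 57·0.28 ≈ 20 successes are expected, which is also why the pooling rule is needed.

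Add one sentence saying that treatment changes after randomisation are kept out of the primary model, tabulated by arm, and used only in labelled supportive analyses.

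The cost is wording only. Centre and baseline BDI-II are already recorded for every participant, and the sample size need not change. Fixing the model in advance also removes any choice between adjusted and unadjusted results after the data are seen.

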### Benefits, risks and compensation of participants

Participants assigned to the intervention group will receive personalized nutritional guidance from a registered nutritionist who will promote adherance to the MedDiet, which has been shown to have health benefits in several chronic diseases that are commonly co-occurring with MDD. At the conclusion of the study, results and findings will be shared with all participants. If the study hypothesis is confirmed, individuals in the control group will be provided with information on how to improve their adherence to the MedDiet. Aside from the standard risks associated with blood sample collection, no additional risks are expected with the proposed intervention. No financial or gift compensation will be provided.

### Discontinuation of participation and missing data

Participants discontinuation is expected to occur in the following scenarios: hospitalization during the trial, development of conditions that forbid adherence to the MedDiet, diagnosis of a disease that is incompatible with the intervention, or initiation of another nutritional intervention. Baseline data from participants who are excluded after baseline assessment will be included in the sample characterisation.

Missing data from participants that don’t complete all the steps planned in the trial will be analysed following an ITT approach.

Motives of participant exclusion or abandonment will be documented and reported if the information is available.

Due to the nature of the intervention, the promoting adherence to the MedDiet, negative reactions are not expected.

### Dissemination policy

The results of the study will be disseminated to interested parties, including the professionals involved in the study’s design and implementation, the scientific community, mental health professionals, and the public at large. A seminar to present the results and conclusions will be held at the end of the data analysis, with additional presentations taking place at the recruitment centres. The findings of the study will be shared with the scientific community through (1) presentations at conferences and meetings related to nutrition, medical nutrition, psychiatry, psychology, and epidemiology; (2) publication in scientific peer-reviewed journals; and (3) a final report, which is a requirement of the funding entity for the study.

## Discussion

Even though treatments are available, about one-third of patients with MDD don’t find sufficient relief of symptoms even after several treatment approaches [2]. Increased inflammation biomarkers have been associated with a higher risk of developing MDD and diminished efficacy of conventional treatments [2, 3].

This study aims to understand if promoting adherence to the MedDiet, as an adjuvant strategy in the treatment of MDD, is effective to decrease symptoms of depression in patients diagnosed with MDD with high levels of inflammation biomarkers, namely elevation of CRP and/or IL-6 at baseline.

### Strengths

This study will be the first RCT to evaluate the effect of a nutritional intervention with anti-inflammatory properties, as an adjuvant in the treatment of MDD, in individuals diagnosed with MDD and elevated CRP and/or IL-6 biomarkers. The selection of individuals with elevated inflammation biomarkers, will potentially target patients that might benefit more from the proposed intervention.

As participants will be recruited during their routine medical appointments and the intervention will take place near recruitment centres, the trial conditions will closely resemble routine care, reducing the potential for bias. The use of a passive control group that will only receive TAU will allow for an evaluation of the impact of the proposed intervention compared to standard care. The cost-effectiveness analysis will provide information on the scalability of the proposed treatment.

### Limitations

There is a potential challenge in recruiting a sufficient sample size for this study, as the condition of having elevated CRP and IL-6 levels will increase the number of participants needed to be invited. Similar difficulties have been identified in a previous study [24]. To address this, participant recruitment and data collection will happen simultaneously in three hospitals, with more recruitment centres planned to be added as the trial progresses.

Due to the nature of the study, which involves promoting adherence to a specific diet, it will not be possible to blind the participants or researchers delivering the intervention to allocation groups. To minimize the resulting bias, the researchers responsible for statistical analysis will be blinded to allocation groups. Using the PREDIMED-MEDAS questionnaire to assess MedDiet adherence and measuring inflammation biomarkers at each assessment point will help to identify any associations between alterations in diet adherence, inflammation biomarkers, and changes in depression symptoms.

The study design involves a passive control group that will receive no active intervention besides TAU. This approach eliminates the risk of comparing two effective interventions, but increases the risk that differences found between groups could be due to differences in intervention intensity between groups.

## Conclusion

This study will contribute to the understanding of the role of inflammation and nutrition in the treatment of MDD, in a group of patients with a lower remission rate with usual treatments, with potential gains in terms of improving health and reducing healthcare costs.

## Data Availability

Data available at clinicaltrials.gov (NCT05745194).

## List of abbreviations

BDI-II: Beck Depression Inventory II
CRP: C-Reactive Protein
IL-6: Interleukin 6
MDD: Major Depressive Disorder
MedDiet: Mediterranean Diet
RCT: Randomized clinical trial
TAU: Treatment as usual
TRD: Treatment Resistant Depression
